### 2.11. Feasibility for Wider Application

Prior to the RCT proposed herein, a pilot study of a similar intervention arm design was undertaken. That is, early career clinicians and clinical trainees administered the HRTP to racialized clients under the supervision of clinical psychologists. Below is feasibility data from the pilot study’s early clients and clinicians. Data collection for the pilot study was nearly complete at the time of this manuscript’s submission.

*Implementation* refers to the degree to which a new treatment can be successfully delivered within a given setting (Bowen et al., 2009). Within the pilot study conducted preceding this proposed study, implementation was operationalized in terms of time to completion. That is, were therapists able to deliver the HRTP within a reasonable time frame? Within the pilot study, therapists took 13.66 weeks on average to complete the HRTP with clients (*n* = 10 completers), which is well within the expected 3–4-month time frame.

The team also considered *practicality* or the extent to which the new treatment can be carried out using existing means, absent external intervention. As such, practicality was operationalized in terms of (1) therapist ease in terms of adhering to the protocol without the need for deviation; and (2) client homework completion (as a proxy for the client’s abilities to carry out important protocol activities). The said elements were largely measured using session notes. More specifically, therapists completed session progress notes within 24 h of each HRTP session. Each note asked therapists to reflect on several items, including but not limited to, “Were you required to deviate from the treatment protocol approved agenda in any way during the session? If so, please explain how you deviated and why?” There is also space for the therapist to indicate homework completion for the session on a 4-point scale: “completed”; “partially completed”; “not attempted”; or “not applicable”.

On therapist adherence to the assigned protocol, within the pilot study (*n* = 14 client cases which included 10 completers and 4 early dropouts) 71.4% of sessions in the Stabilization phase, 66.7% in the Healing phase, and 62.5% in the Empowerment phase required no deviation on the part of therapists to meet client needs. Moreover, it is important to note, many of the deviations reported related to either (i) allocating more or less time to an existing protocol agenda item than was suggested in the protocol; or (ii) rearranging protocol agenda items to better fit the natural flow of the session. Few of the deviations reported included the therapist feeling obligated to look beyond the protocol or introduce non-HRTP interventions to meet client needs (between 9.5 and 17.6%, depending on the treatment phase). On the matter of client homework completion, clients in the pilot study had a completion rate of 51.2% in the Stabilization phase, 56.9% in the Healing phase, and 62.5% in the Empowerment phase. There was also an additional 12.2%, 35.3%, and 32.5% partial completion rate for the different phases, respectively.

Conversely, *acceptability* is defined as the perception of the new treatment by implementation stakeholders (Bowen et al., 2009). As such, acceptability was operationalized in terms of (1) therapist comfort with delivering the protocol, as well as (2) client satisfaction with the HRTP. On therapist comfort, part of each session note reflection required therapists to rate their level of comfort in terms of delivering the session material on a 5-point scale: “1—extremely uncomfortable”, “2—slightly uncomfortable”, “3—neither comfortable or uncomfortable”, “4—slightly comfortable”, or “5—extremely comfortable”. And finally, as an element of each client’s week 20 data collection (note, within the pilot study we conducted follow-up at 20 weeks, not 28), clients were asked “If you had a family member or close friend that suffered from racial trauma, would you recommend they complete the HRTP. Why or why not?”.

On therapist comfort with delivering the HRTP (*n* = 14 client cases which included completers and early dropouts), the mean comfort rating was 4.25 (*SD* = 1.01) within the Stabilization phase, 4.59 (*SD* = 0.83) in the Healing phase, and 4.60 (*SD* = 0.81) in the Empowerment phase. As such, throughout the delivery of the HRTP, the therapists’ comfort levels averaged somewhere between “slightly comfortable” and “extremely comfortable”. On whether or not pilot study clients opted to recommend the HRTP to family and friends, 100% of the completers who participated in an exit questionnaire (*n* = 7 completers) noted that they “would recommend” the protocol to loved ones in future.

### 2.12. Statistical Analysis

Descriptive statistics, including means, standard deviations, and frequencies, will be calculated for continuous primary and secondary outcomes. Differences in primary and secondary outcomes, including TSDS, RTS, change in symptoms, and therapeutic experiences, will be examined using a two-way mixed ANOVA with two or three within-subject levels of time (pre-test, post-test, and follow-up) and two between-subject levels of condition (HRTP and control). When there is evidence of sphericity violation, we will use the Greenhouse–Geisser correction (Greenhouse & Geisser, 1959). It is predicted that participants’ TSDS and RTS scores will decrease significantly over the course of the treatment. It is also predicted that TSDS and RTS scores at follow-up will be the same or lower than at the end of the treatment.

Both the short-term and long-term efficacy of the HRTP will be examined during the treatment (week 0, 4, 8), at the end of the treatment (week 12), and 4 months after the treatment (week 28). Assessment will take place at four time points for the treatment group (HRTP therapy; weeks 0, 4, 8, 12, and 28; see Table 1 for participants’ assessment schedule) and only two time points for the control TAU group (T0 and T4; see Table 1 for participants’ assessment schedule). Analysis will compare standard mean differences (SMDs) between the time points for the treatment group (weeks 0, 12, and 28) and the control group (weeks 0 and 12). Analyses will entail intent to treat (ITT) and include participants with pre-treatment and the last time point available as long as they attended at least one treatment session. We examine significant levels for the analysis as well as effect sizes. A significance level of *p* < 0.05 will be used for all tests.

For each outcome of interest, we will identify any significant Condition × Time interactions. When no interaction is found, significant main effects will be reported. Partial eta-squared (η2) was used to measure effect sizes for the ANOVAs. When significant interactions are found, post hoc tests of simple main effects will be used to examine the differences, *p* values will be included for all post hoc tests, and 95% confidence intervals (CIs) will be used for all *p* values less than 0.05. Additionally, we will conduct comparisons of baseline data for completers and non-completers. Subgroup analysis will be based on age, gender, and levels of racial stress and trauma.

The secondary outcomes will compare the quality of the therapeutic experiences throughout the treatment group (HRTP therapy; weeks 4, 8, 12), as well as comparing the quality of the sessions between the treatment and control groups (week 12). The strength of the therapeutic alliance between the participants and therapists (Helping Alliance Questionnaire; Luborsky et al., 1996) will be evaluated, as will whether or not the participants perceived any microaggressions in their sessions (Racial Microaggressions in Counselling Scale; Constantine, 2007).

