### 1.4. The Goals of the Current Study

The primary objective of this paper is to describe a randomized controlled trial that will compare the efficacy of the HRTP for people of colour suffering from racial trauma compared to a control condition of treatment-as-usual (TAU) in reducing the severity of racial trauma and related symptoms, as well as improving functioning. This paper will provide preliminary feasibility evidence in terms of implementation, practicality, and acceptability for clients and therapists. Additionally, we will outline methodological approaches to trial design, the research population, and treatment protocols. That is, methodological approaches which could serve as inclusive and viable models for engaging in clinical research related to racialized populations. Specifically, the proposed trial will examine: (a) whether the administration of the HRTP will result in a clinically significant reduction in racial trauma symptoms in participants compared to the TAU control group, and (b) whether any clinically significant reduction in racial trauma symptoms is maintained long-term (i.e., 4 months after the intervention).

It is hypothesized that the completion of the 12-session HRTP will result in a clinically significant improvement in participants’ racial trauma symptoms and severity, as well as improved functioning. It is also hypothesized that these changes will be greater than changes in the control conditions and will be maintained 4 months following the completion of the intervention.

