### 2.9. Primary Outcomes

Three primary outcomes will be measured at five time points for the treatment group (weeks 0, 4, 8, 12, and 28) and twice for the TAU control group (weeks 0 and 12). See Table 1 for the participants’ assessment schedule. Of note, there will be a differential assessment schedule for TAU versus HRTP participants. That is, HRTP participants are assessed on three more occasions than those in the TAU group. Two of these additional assessment periods are included within the intervention arm’s active treatment phase (weeks 4 and 8) to better understand how each HRTP phase impacts healing/racial trauma symptom severity. Week 4 roughly translates to the participants transitioning to the Healing phase and week 8 the Empowerment phase. Further, those in the control arm have no need for a post-treatment follow-up as upon receiving TAU, they may be immediately enrolled within the treatment group to receive the HRTP.

The *Racial Trauma Scale* (RTS; Williams et al., 2022c) is a 30-item clinical measure which examines the severity of traumatic symptoms due to racism. More specifically, the RTS asks individuals to “think about all the times when you have heard about, seen, or experienced racial discrimination” and how much they have been bothered by resultant thoughts, behaviours, or symptoms on a 4-point scale (where 1 is “not at all” and 4 is “extremely”). Of note, within this study specifically, when completing the RTS, clients will be asked to rate symptoms as per their lived experience over the previous month/30 days. An RTS total score is calculated by summing all item ratings together. Moreover, subfactors of the RTS include “Lack of Safety”, “Negative Cognitions”, and “Difficulty Coping”. Higher RTS total and subfactor scores indicate greater symptom distress. In consideration of the RTS’s convergent validity, RTS responses were found to be highly correlated with several measures of trauma, including the *PTSD Checklist for the DSM-5* (PCL-5; r = 0.79) and the *General Ethnic Discrimination Scale* (r = 0.76). The RTS was developed for and tested with diverse ethnoracial populations. The RTS also has excellent reliability (α = 0.97; Williams et al., 2022c).

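### The two-arm ANOVA with a follow-up level cannot test Condition × Time, because TAU has no week-28 assessment; the plan also states the controls' access to HRTP in two incompatible ways

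*Protocol article*

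**What the plan says.** All references are to the protocol article.

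- **Model (section 2.12).** Primary and secondary outcomes are to be analysed with a "two-way mixed ANOVA with two or three within-subject levels of time (pre-test, post-test, and follow-up"), with HRTP and control as the two between-subject levels. The next sentence adds: "When there is evidence of sphericity violation, we will use the Greenhouse–Geisser correction". For each outcome, "we will identify any significant Condition × Time interactions".
- **Schedule.** Section 2.9 measures the primary outcomes at weeks 0, 4, 8, 12 and 28 in the HRTP arm but only "twice for the TAU control group (weeks 0 and 12"). Section 2.12 compares standardised mean differences between time points for "the treatment group (weeks 0, 12, and 28) and the control group (weeks 0 and 12"). In Table 1 the TAU entry at week 28 lists no measures. It says that controls will by then have left the study or begun HRTP.
- **Long-term aim.** Section 1.4 asks "whether any clinically significant reduction in racial trauma symptoms is maintained long-term". Section 2.12 says "Both the short-term and long-term efficacy of the HRTP will be examined during the treatment" and goes on to list week 12 and week 28.
- **Analysis set (section 2.12).** The intention-to-treat analysis will "include participants with pre-treatment and the last time point available", provided that they attended at least one session.
- **Access to HRTP for controls.** Section 2.4 offers it once TAU and the 4-month follow-up are both complete. Section 2.9 says controls need no follow-up because they can enter HRTP directly after TAU.

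**The concern.** The model sentence names follow-up as a time level and crosses it with both arms, but the schedule collects nothing from TAU at follow-up. A three-level Condition × Time test needs a control mean at week 28, and none will exist.

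Two consequences follow. First, the analyst would find that the three-level model fails or collapses to the two-level one, and would have to choose a remedy after the data are in. Second, a reader could take a week-28 result labelled long-term efficacy as a randomised finding, when it can only be a before-and-after description within one arm. Section 2.9 discloses that the schedules differ but not what this does to the conclusion.

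The wording on the last available time point adds a conditional risk. If it were used to supply the endpoint or to fill the empty cell, HRTP at week 28 would be set against TAU at week 12.

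The crossover contradiction affects participants directly. It also decides whether an untreated control group could exist at week 28 at all.

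**Working it through.** **Inputs.** Two conditions and up to three time levels (section 2.12); TAU assessed at weeks 0 and 12 only (sections 2.9 and 2.12, Table 1); 48 per arm and 20% attrition (section 2.2).

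**1. Cells.** Write g = 1 for HRTP and 0 for TAU. The 2 × 3 model has six parameters: μ, α (condition), β12 and β28 (time), γ12 and γ28 (Condition × Time).

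| | Week 0 | Week 12 | Week 28 |
|---|---|---|---|
| TAU | μ | μ + β12 | μ + β28 (never observed) |
| HRTP | μ + α | μ + α + β12 + γ12 | μ + α + β28 + γ28 |

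With the TAU week-28 cell empty, β28 and γ28 appear only as the sum β28 + γ28, so neither can be separated from the other.

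**2. Rank check.**

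| Layout | Observed cells | Parameters | Rank |
|---|---|---|---|
| Full 2 × 3 | 6 | 6 | 6 |
| 2 × 3 without TAU week 28 | 5 | 6 | 5 |
| 2 × 2, weeks 0 and 12 | 4 | 4 | 4 |

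In the middle layout γ12 is estimable and γ28 is not. The interaction has (2 − 1) × (3 − 1) = 2 nominal degrees of freedom. One survives, and it is the same week 0 to 12 contrast as in the 2 × 2 model.

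**3. Complete-case fitting.** A classical repeated-measures ANOVA on participants observed at all three times keeps 0 controls, so the condition factor disappears.

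**4. What week 28 can give.** The HRTP change from week 12 to week 28, (β28 + γ28) − (β12 + γ12), is estimable but has no control counterpart.

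**5. Sphericity correction.** The lower bound of the Greenhouse–Geisser epsilon is 1/(k − 1): 1.0 for k = 2, so it never corrects, and 0.5 for k = 3. The correction therefore matters only with three or more levels. This supports the view that a three-level model is planned but does not prove it.

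**6. Last scheduled assessments.** Week 28 − week 12 = 16 weeks between the arms.

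**7. Precision of the HRTP-only change (illustrative).** The documents give no correlation between weeks 12 and 28, so 0.5 to 0.8 is assumed, with equal SDs at the two weeks. The 95% half-width in SD units is t(0.975, n − 1) × √(2(1 − ρ)) / √n. With 20% attrition, 48 × 0.8 = 38.4, taken as 38.

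| n | ρ = 0.5 | ρ = 0.7 | ρ = 0.8 |
|---|---|---|---|
| 38 | 0.329 | 0.255 | 0.208 |
| 48 | 0.290 | 0.225 | 0.184 |

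**8. Crossover rules side by side.** Section 2.4: HRTP after the 4-month follow-up, about week 28. Section 2.9: directly after TAU, about week 12. Table 1: controls withdrawn or already on HRTP by week 28. The first cannot hold together with the other two.

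**The case against.** The strongest reply is that the text can be read sensibly: two time levels for the arm comparison and a third for HRTP alone, as the per-arm week list in section 2.12 suggests. Objective (b) concerns maintenance only, and section 2.12 predicts follow-up scores no higher than at end of treatment, so no between-arm comparison at week 28 is ever stated. The sphericity correction could serve within-HRTP analyses, which have up to five time points. The sentence on the last available time point says who is included, not which weeks are compared. The randomised week 0 to 12 result is not biased, and a model with no controls would fail visibly.

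Much of this stands. The primary comparison is intact, the sphericity argument is only supporting evidence, and the endpoint mismatch is a risk and not a stated plan. The crossover contradiction also changes no scheduled analysis, since neither version includes a TAU assessment at week 28.

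The sensible reading does not repair the text, however. An HRTP-only model has no condition factor and so is not the two-way mixed ANOVA that the sentence specifies. Nor is this detail that could be left to an analysis plan: the article states both the model and the schedule, and the two are incompatible.

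**Conclusion.** The concern holds. As written, the three-level, two-arm Condition × Time test cannot be carried out: one of six cells is empty by design, and 1 of 2 interaction degrees of freedom is estimable. This is structural and does not depend on the sample size, effect size or attrition. The week 0 to 12 randomised comparison is unaffected, and maintenance can still be described from HRTP data. What changes is the conclusion available at week 28, which is uncontrolled. The contradiction between section 2.4 and both section 2.9 and Table 1 on when controls may receive HRTP also holds. Only the half-widths of 0.18 to 0.33 SD rest on assumptions (the correlations and equal SDs); they show the likely precision and are not part of the defect. The point should be fixed, but it does not threaten the main comparison.

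**What to change.** 1. State in section 2.12 that the Condition × Time ANOVA uses weeks 0 and 12 only. For that comparison, define the last available time point as no later than week 12 in both arms, and do not carry the TAU week-12 value into a follow-up level.
2. Report the week 28 minus week 12 change for HRTP only, labelled uncontrolled, with a 95% confidence interval whatever its p value. Section 2.12 promises intervals only for p values below 0.05, so the predicted result of unchanged scores could come without one. Do not infer maintenance from non-significance alone, and make no between-arm claim of long-term efficacy.
3. Use one crossover rule throughout. The simplest course is to align section 2.4 with section 2.9 and Table 1.

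The cost is wording in sections 2.12 and 2.4: no new data, no change in sample size and no delay in HRTP for controls. The price is that week 28 must be presented as uncontrolled. Adding a TAU week-28 assessment before access to HRTP would be a design choice for the sponsor and is not needed for this fix.

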### 2.2. Sample Size, Randomization, and Allocation

A sample of 96 participants (48 per group) is needed for an 80% probability to identify a difference between the treatment and control group. The power analysis for the sample size estimation was based on the means, standard deviations, and clinical cut-off for the primary outcomes (RTS, TSDS; Williams et al., 2022c, 2023b). Drawing on previous research, we hypothesized a standard mean difference of between 0.36 and 0.52, between the treatment and control group, which translates to a 10–20% decrease in the primary outcomes (i.e., RTS, TSDS) for individuals at the endpoint of treatment. Given these effect estimates, with an alpha of 0.05, an 80% power, and a 20% attrition, we estimated a sample size of approximately 96 (48 per group) will be needed. This randomized controlled trial will use an ANOVA and t-test (alpha error level = 5%, two-sided) for independent samples.

This sample size will require tailored recruitment efforts, community partnerships, and culturally safe retention strategies throughout the trial. Given differential attrition rates for racialized communities, the research team will spend additional time at intake discussing barriers to participation, issues with attendance, and address any participant concerns. Additionally, the research team will offer flexible session meeting times (e.g., evenings and weekends), and telephone check-ins as needed. The research team shall also compensate participants for both their completed sessions and batteries of measures.

In terms of blinding, the trial research team will be unaware of the group allocation. This includes the principal investigator and project coordinator who are overseeing the trial implementation, research assistants who will support recruitment and data collection, and the statistician conducting the analysis. See Figure 1 for the participant flow diagram of the trial.

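### Maintenance at week 28 is a no-worsening claim, but the plan offers only difference tests, no criterion for the planned effect sizes, and intervals only when p < 0.05

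*Protocol article*

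**What the plan says.** Section 1.4 gives the trial two questions. The second is "whether any clinically significant reduction in racial trauma symptoms is maintained long-term (i.e., 4 months after the intervention", and the hypothesis paragraph that follows repeats it.

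Section 2.12 turns this into a prediction for the two racial-trauma scales: "scores at follow-up will be the same or lower than at the end of the treatment". On analysis, the same section says:

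- Outcomes "will be examined using a two-way mixed ANOVA with two or three within-subject levels of time (pre-test, post-test, and follow-up") and two levels of condition. Follow-up simple-effects tests come only after a significant Condition × Time interaction.
- "A significance level of *p* < 0.05 will be used for all tests". Section 2.2 describes the tests as two-sided ("alpha error level = 5%, two-sided) for independent samples").
- "95% confidence intervals (CIs) will be used for all" p values below 0.05. This stands in the sentence on post hoc tests.
- "Analysis will compare standard mean differences (SMDs) between the time points for the treatment group (weeks 0, 12, and 28"), and "We examine significant levels for the analysis as well as effect sizes".
- Participants are analysed with their baseline and last available time point, provided they attended at least one session.

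Section 2.9 and Table 1 schedule week-28 measures for the HRTP arm and none for TAU. The article gives no margin or other criterion for calling gains maintained.

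**The concern.** A prediction that scores stay level or fall needs evidence that any rise is small. A difference test asks whether the change is distinguishable from zero. When it is not significant, the data may show no relapse, or there may be too few people to see one. An interval for the change separates these two cases, and the stated rule drops the post hoc interval in exactly that situation.

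The incentive also runs the wrong way: the fewer clients who return at week 28, the easier it is to find no significant worsening. At stake is the durability claim in objective (b). The week-12 comparison of HRTP with TAU is not affected.

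**Working it through.** **The plan's own figures.** The article gives no power or precision for the week 12 to 28 change, so there is none to reproduce. Its total of 96 belongs to the between-arm comparison. It does not follow from the stated inputs: 2 × (1.960 + 0.842)² / 0.52² gives 59 per arm before attrition, against 48. That is a separate matter, and only the planned 48 per arm is used here.

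**Inputs from Section 2.2.** 48 HRTP participants; 20% attrition, so 48 × 0.8 = 38.4, taken as 38; hypothesised between-arm SMD 0.36 to 0.52, half of which is 0.18 to 0.26; two-sided 5%.

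**Assumptions.** The correlation r between week-12 and week-28 scores is not given and is set at 0.5, 0.7 and 0.8. The SD is taken as equal at both weeks and equal to the SD behind the SMD.

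**Step 1: power of a paired t test, week 28 against week 12, HRTP arm.** The SD of the change is √(2(1 − r)) = 1.000, 0.775, 0.632. Then d_z = rise / √(2(1 − r)), with noncentrality d_z × √38 on 37 degrees of freedom.

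| Rise (SD) | r = 0.5 | r = 0.7 | r = 0.8 |
|---|---|---|---|
| 0.18, power | 19% | 29% | 40% |
| 0.18, missed | 81% | 71% | 60% |
| 0.26, power | 35% | 52% | 69% |
| 0.26, missed | 65% | 48% | 31% |

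Power of 80% needs d_z of about 0.467, which is a rise of 0.47, 0.36 or 0.30 SD. That is close to the size of the whole hypothesised between-arm effect.

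**Step 2: sensitivity.**

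- If all 48 return, power is 23% (0.18) and 42% (0.26) at r = 0.5, and 35% and 63% at r = 0.7.
- With 38, power passes 50% at r of about 0.68 for a rise of 0.26 and about 0.85 for 0.18.
- If the within-arm gain were 0.8 SD (an assumption; the article gives none), loss of half, 0.40 SD, would be detected with power 67%, 87% and 97% at r = 0.5, 0.7 and 0.8.

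**Step 3: precision.** The 95% half-width is 2.026 × √(2(1 − r)) / √38 = 0.33, 0.25 and 0.21 SD. A non-significant result is therefore compatible with a rise of at least that size when the observed change is zero, and with more when it is positive.

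**Step 4: last available time point.** If week 12 stands in for week 28 in 20% of clients, their change is zero and the mean change shrinks to 0.8 of its value: 0.26 becomes 0.208 and 0.18 becomes 0.144. Power with n = 48 is then 35% and 19% at r = 0.5, about the same as with 38 observed. The estimate is now biased towards no relapse, and the gain in n is only apparent.

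**Step 5: the post hoc gate.** Simple-effects tests open after a significant Condition × Time interaction. With no TAU score at week 28, an interaction that includes follow-up cannot be formed, so the stated sequence does not lead to the week 12 to 28 contrast.

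**The case against.** The strongest reply is that the article never says a non-significant test will be read as maintenance. Its sentence is a prediction, not a decision rule. A reader might infer that loss of half the benefit would usually pass as maintained, and the document does not support that, for three reasons.

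- No such reading of the test is stated.
- Whether half the benefit is usually missed depends on a correlation that the article does not give. At a rise of 0.26 SD the odds are about even at r = 0.7, and detection is likelier than not at r = 0.8.
- The SMD of 0.36–0.52 is a difference from TAU, which is itself 12 sessions of established therapy. The change within HRTP could be larger, and losing half of a larger gain is easier to detect (Step 2).

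A reader might also infer that difference tests are the only evidence planned. They are not: standardised differences across weeks 0, 12 and 28 and effect sizes will be reported, and a relapse could be visible there. The interval restriction is tied to the post hoc tests and does not clearly govern these quantities.

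Finally, an article may leave a margin to the full protocol or analysis plan, so its absence alone would not be a finding.

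What stands is narrower. The article itself fixes the prediction, the family of tests, the significance level for every test and the interval rule. Together these do not fit a no-worsening objective, and the effect sizes carry no threshold that would settle it.

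**Conclusion.** The point holds as a mismatch between objective (b) and the inference stated for it. Under the plan as written, a non-significant week 12 to 28 change in about 38 clients would not by itself show maintenance, and its post hoc result would carry no interval to say what relapse remains possible.

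The miss rates in Step 1 rest on the assumed correlations, equal SDs, 20% attrition and half the between-arm SMD as the relapse of interest. They illustrate how weak the test is and do not forecast what the trial will conclude. The logical point does not depend on them. Because TAU has no scheduled week-28 score, any conclusion on durability is within the HRTP arm, whichever criterion is used.

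**What to change.** In Section 2.12, replace the prediction with a criterion:

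1. Report the HRTP week 28 minus week 12 change in RTS and in TSDS with its 95% confidence interval, whatever the p value and without waiting for an interaction test.
2. Use observed week-28 scores, not week 12 carried forward.
3. Fix a margin of worsening for each scale in advance, with its justification. It should be a set value; a fraction of the gain later observed would move with the data.
4. Claim maintenance on a scale only if the upper limit lies below its margin. Otherwise conclude *maintenance not shown*.
5. State that the conclusion is within-arm.

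This costs a few sentences and no new data. The price is that a truly durable effect may often remain unproven. Purely for illustration, with margins of 0.18 and 0.26 SD, no true change and 38 clients, Φ(margin × √38 / √(2(1 − r)) − 1.96) gives a 20–42% and a 36–72% chance of success over r = 0.5–0.8. For 80%, the completers needed are ((1.960 + 0.842) × √(2(1 − r)) / margin)²: 243 to 97 for a margin of 0.18, and 117 to 47 for 0.26. The planned arm falls short of all of these except the last, which it would meet only with 47 of its 48 clients returning.
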